### Sample

3.2

Patients will be stratified into two groups dependent on their exposure to DSME. The primary cohort is those who have a READ code confirming they have ‘*ever’* received DSME (*n* = 21 298) (Table 1 lists the Med Code IDs for exposure to DSME). Guidelines recommend DSME for all patients newly diagnosed with type 2 diabetes.^5^ To allow sufficient time for exposure to DSME and to account for immortal time bias^21^ any hospitalisations or deaths within the first 12 months of diabetes diagnosis will be excluded in both ever and never DSME groups as it is likely that there will be a period during the 12 months in which patients have not had the opportunity to be exposed to the intervention.

**TABLE 1 dom16257-tbl-0001:** DSME Med Code IDs.

Med Code ID	Term
2 533 102 013	Attended diabetes structured education programme
5.32331E+14	Diabetes structured education programme completed
5.46001E+14	Attended XPERT diabetes structured education programme
5.46221E+14	DESMOND diabetes structured education programme completed
5.46291E+14	XPERT diabetes structured education programme completed
6.84397E+15	Attended diabetes structured education programme
8.09822E+15	Attended expert patient education versus routine treatment diabetes structured education programme
8.09824E+15	Attended XPERT (expert patient education versus routine treatment) diabetes structured education programme
8.09835E+15	Expert patient education versus routine treatment diabetes structured education programme completed
8.09837E+15	XPERT (expert patient education versus routine treatment) diabetes structured education programme completed
1.21156E+16	Remote diabetes structured education and support programme commenced
1.21156E+16	Remote diabetes structured education and support programme completed

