### Data selection

3.3

To minimise the impact of incorrect information or flawed subject selection the ‘*ever’* cohort will be matched at baseline to patients who have ‘*never’* received DSME (*n* = 584 312). Age,^22^, ^23^ age at diagnosis and diabetes duration^22^, ^24^, ^25^, ^26^ are the most important predictors of one‐year mortality in type 2 diabetes.^27^ Every decade of earlier diabetes diagnosis is associated with 3–4 years of lower life expectancy.^24^

Cohort analysis, systematic review and meta‐analysis have considered the association between diabetes and sex, demonstrating that women generally have a higher risk of coronary heart disease and all‐cause mortality (58%) compared to men and a 13%–17% greater risk of all‐cause mortality.^28^, ^29^ Moreover, the additional likelihood of developing cancer and the higher risk of premature mortality from having diabetes is more pronounced in women.^30^

Patients will therefore be matched at baseline for age ± 5 years, age at diagnosis ±5 years, diabetes duration ±1 year and sex who are present in the dataset from the same start year or earlier.

This study will adopt an intention‐to‐treat analysis, with patients contributing only to the original exposure group in which they have been assigned, irrespective of when they receive DSME. Baseline for the ‘ever’ group and their matched controls will be the date of DSME intervention. Patients will remain exposed until they are censored by death, leave the GP practice, leave a GP practice which contributes to CPRD data or end of the study period (29 March 2021).

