### Study size

3.5

The study sample includes all patients in CPRD Aurum available during the study period who meet the inclusion criteria. A feasibility search on Aurum identified people meeting the study inclusion criteria (*n* = 605 710). A priori calculation of the sample size whilst presenting some uncertainty cannot be determined beforehand as the sample size will be reduced by inclusion of confounding variables and exclusion of some individuals.^19^ The sample size included in this study from feasibility counts is far larger than usually considered in hypothesis testing situations such as those proposed in this study. This gives us confidence we have sufficient sample size in this study for a reliable assessment of the research questions. Nevertheless, as an example, the 21 398 ‘*ever*’ patients and 584 312 ‘*never*’ patients identified would be sufficient to detect a difference in the proportion hospitalised (main outcomes) of approximately 1.9% with a power of 80% and a significance level of 5%.

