### Statistical methods

3.6

Baseline characteristics of participants will be summarised using descriptive statistics (mean, median, interquartile range and standard deviations as appropriate). We will also summarise total number of hospital admissions and length of stay by age, age at time of diabetes diagnosis, diabetes duration, ethnicity and IMD decile.

The primary cohort is those who have ‘*ever*’ received DSME in each of the 10 years in the study to identify hospital admissions and cause of death during follow‐up. We will additionally have a matched diabetes cohort who have ‘*never’* received DSME to provide comparison (rate ratios).

An initial crude analysis will compare the proportion of hospitalisations and deaths between *ever* and *never* DSME groups. Chi‐squared tests will be used to compare these proportions. Similar tests will be used for subgroup analysis and alternative outcomes (cause‐specific hospitalisations and mortality).

Number of hospital admissions will be calculated to estimate relative risk of admissions and mortality by all‐cause and cause‐specific using a mixed Poisson model. Should the data be over dispersed a negative binomial mixed model will be adopted.

A Cox proportional‐hazards model will be used to measure time to event for first hospital admissions and mortality with the proportional hazards assumption checked using Kaplan—Meier curve plots and Schoenfeld residuals tests. If the proportional hazards assumption does not hold, then alternatives such as restricted mean survival times models will be used.

Baseline covariates will be reported among the ‘ever’ and ‘never’ groups, and a statistical test will be applied to see whether these differ significantly. These will be examined in multivariate models. We will address potential issues with confounding by indication firstly within the study design in which individuals in the ever group will be matched at baseline for age, sex, diabetes duration and age at diagnosis to individuals in the never group. All models will be adjusted a priori for CCI, IMD, HbA1c, BMI, smoking status, lipid level and SBP during multivariate analysis.

Statistical analysis will be conducted using R version 4.4.1. Alpha level will be set at 5% for statistical significance.

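### 'Never' controls are picked by what happens after their index date, which contradicts the intention-to-treat claim and tilts the mortality comparison slightly towards DSME

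*Protocol article*

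**What the plan says.** All references are to the protocol article.

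- **Groups (section 3.2).** "Patients will be stratified into two groups dependent on their exposure to DSME". 'Ever' means a DSME code in the record.
- **Controls (section 3.3).** They are drawn from patients who have 'never' received DSME, given as 584 312. They are matched on age, age at diagnosis, diabetes duration and sex, among those "who are present in the dataset from the same start year or earlier".
- **Time zero (section 3.3).** Baseline for the 'ever' "group and their matched controls will be the date of DSME intervention".
- **Analysis principle (section 3.3).** Intention-to-treat, "with patients contributing only to the original exposure group in which they have been assigned, irrespective of when they receive DSME".
- **End of follow-up (section 3.3).** "Patients will remain exposed until they are censored by death, leave the GP practice, leave a GP practice which contributes to CPRD data", or the end of the study. There is no rule for a control who later attends DSME.
- **Immortal-time safeguard (section 3.2).** "any hospitalisations or deaths within the first 12 months of diabetes diagnosis will be excluded in both ever and never DSME groups".

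**The concern.** Intention-to-treat fixes a patient's group at time zero and ignores what the patient does afterwards. A 'never' group cannot be fixed at time zero, because membership is known only when the record closes.

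Take two patients, both without DSME on an index date in 2013. One attends in 2016, so is 'ever' and cannot serve as a 2013 control. The other dies in 2014 without attending, so can. The first had to survive until 2016 to be removed. Dropping such patients takes survivors out of the comparator, raises its death rate and makes DSME look protective even if it does nothing.

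The stated safeguards do not reach this. The 12-month exclusion runs from diagnosis, not from the index date. Starting 'ever' follow-up at the DSME date does remove classic immortal time from the attenders, but it does not change who is left among the controls. The covariate adjustment in section 3.6 uses baseline values and cannot undo selection on survival after baseline. Mortality is a named objective (section 2) and the bias runs in the hoped-for direction.

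**Working it through.** **1. Is 'never' really a whole-record definition?** Section 3.5 gives 21 398 'ever', 584 312 'never' and 605 710 in total. 21 398 + 584 312 = 605 710 exactly, so the two groups exhaust the pool and no one is in both. Overall uptake is 21 398 / 605 710 = 3.5%. (Section 3.2 prints 21 298, which would give 605 610 and does not fit the total; this does not affect the point.)

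**2. Size of the bias on mortality with no true DSME effect.** The document gives no death rate and no rate of later uptake, so both are assumed:

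- λ, death rate: 2% or 4% per year;
- T, follow-up from index: 5 or 10 years;
- F, share of patients unexposed at index who would attend within T if none died, with constant uptake rate u = −ln(1 − F)/T.

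Write r = λ + u. Per patient unexposed at index, among those who never attend:

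- deaths: D = λ(1 − e^(−rT))/r
- person-years: P = λ(1 − e^(−rT))/r² + uT·e^(−rT)/r

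Attenders die at rate λ, so the spurious ratio (ever against never) is

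λP/D = λ/r + uT/(e^(rT) − 1).

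Worked case, λ = 0.02, T = 10, F = 3.5%: u = 0.003563, r = 0.023563, λ/r = 0.8488, uT/(e^(rT) − 1) = 0.03563/0.26570 = 0.1341. The ratio is 0.983.

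| F | T=5, λ=2% | T=5, λ=4% | T=10, λ=2% | T=10, λ=4% |
|---|---|---|---|---|
| 1% | 0.995 | 0.995 | 0.995 | 0.995 |
| 3.5% | 0.983 | 0.983 | 0.983 | 0.984 |
| 7% | 0.965 | 0.965 | 0.965 | 0.967 |
| 10% | 0.949 | 0.950 | 0.950 | 0.952 |
| 20% | 0.894 | 0.896 | 0.896 | 0.900 |

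If 3.5% is instead taken as the share actually seen to attend before death or T, F is 3.7% to 4.2% and the ratio is 0.980 to 0.982. The conclusion is the same: about 2%.

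**3. Does an index-date definition remove it?** If everyone unexposed at index is kept as a control, the control rate is λ. If controls are censored at their own DSME date, deaths are D and person-years are (1 − e^(−rT))/r, which again gives λ. A simulation of 4 million people (λ = 3%, T = 10, F = 10%) gave 0.0300 per year for all unexposed, 0.0300 with censoring at DSME and 0.0316 for never-only. The ratio was 0.951, as the formula predicts.

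**4. Cross-check with matching.** A separate null simulation with one matched control per attender (deaths 2.5% per year, 10-year window) gave hazard ratios of 0.997 with whole-record controls and 1.001 with index-date controls when 4% ever attended. That gap is within the simulation error (SE 0.005 to 0.013). With 15% attending they were 0.963 and 1.005. The effect is smaller here than in the table because overall uptake counts all attendance, while F counts only attendance after the index date.

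**The case against.** **The wording can be read the other way.** The intention-to-treat sentence could mean that a control who attends later stays a control, which would be sound. That reading is possible, but it clashes with the label 'never' and with counts that partition the pool exactly. On either reading the sentences in section 3.3 need reconciling.

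**The bias is negligible at documented uptake.** Largely true. Later uptake averaged over the pool should not exceed overall uptake, so 3.5% is towards the upper end for F. A reader might infer from the lower rows of the table that the result could be off by 5% or 10%. The document does not support this. It gives 3.5% overall and, in the Introduction, a national audit attendance figure of 7%. Neither is the rate of later attendance among matched controls. Higher uptake among the recently diagnosed is plausible, since section 3.2 notes that guidelines direct DSME to new diagnoses, but it remains an assumption.

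**The main outcome is hospitalisation.** This also stands. An admission does not stop a patient attending later, so the mechanism that works directly for death works only indirectly for first admission. No size is claimed there.

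**Controls might be dead, deregistered or undiagnosed at index.** A reader might infer this because the start-year condition is the only explicit presence rule. The text does not bear it out: matching at baseline on diabetes duration presupposes a diagnosis, and the censoring rules leave no follow-up for someone already dead or gone. An explicit sentence would be clearer, but this is not a separate fault.

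**Conclusion.** The design point holds. Control eligibility depends on information after the index date, which is incompatible with the intention-to-treat claim in the same section, and the 12-month exclusion does not cure it. The bias on mortality favours DSME.

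With no true effect, the mortality ratio is about 0.98 to 0.995 when 1% to 3.5% of patients unexposed at index attend later. This rests on assumed death rates of 2–4% per year, constant hazards and 5 to 10 years of follow-up. A larger bias needs higher later uptake among matched controls, which the document does not report. Removing later attenders may also sharpen the difference in engagement between the groups, but nothing in the document lets that be sized, and section 4.1 already acknowledges residual confounding. The case for changing the plan is that the stated principle and the stated selection contradict each other, and the cure is cheap.

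**What to change.** 1. Define control eligibility at the index date: no DSME code up to that date, and, stated explicitly, alive, under follow-up and diagnosed.
2. Keep controls in the control group if they attend later. This makes the intention-to-treat description true.
3. Add a sensitivity analysis that censors controls at their own DSME date.
4. Decide whether a later attender who has served as a control may also enter as 'ever' from their own DSME date. If so, amend the one-group sentence in section 3.3 and use a person-clustered (robust) variance.
5. Describe the contrast as attended against not attended by the index date, and align the ever/never wording of the objectives in section 2.

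The cost is an amendment to the wording, matching code that tests DSME status at each index date, and a small amount of variance work, all on the same linked records. The statistical price is slight dilution of any true effect by later attenders among the controls, which should be minor at 3.5% overall uptake.

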## AIMS AND OBJECTIVES

2

The aim of this large retrospective cohort study is to examine the impact of DSME attendance on all‐cause and cause‐specific hospital admissions and mortality in people with type 2 diabetes, utilising linked large UK national datasets to test the hypotheses that DSME attendance impacts all‐cause hospital admissions and mortality.

The specific objectives are to:To describe the epidemiology of patients living with type 2 diabetes who have attended DSME by age, sex, ethnicity, deprivation levels (IMD), HbA1c and baseline Charlson Comorbidity Index in a representative sample of a large cohort of adults who were registered with an English GP between 2011 and 2021.To examine the association between ever or never having attended DSME on all‐cause and cause‐specific hospital admissions, in adults with type 2 diabetes.To examine the association between ever or never having attended DSME on all‐cause and cause‐specific mortality, including but not confined to in‐hospital mortality.To examine the association between ever or never having attended DSME on major adverse cardiovascular events (3P‐MACE); CV death, non‐fatal myocardial infarction (MI) and non‐fatal stroke, in adults with type 2 diabetes.

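### The restricted mean survival time fallback for first hospital admission, under a rule that censors at death, would measure admission-free time as if nobody died

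*Protocol article*

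**What the plan says.** Three parts of the protocol article bear on this.

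- **Data selection (3.3)** defines the end of follow-up: "Patients will remain exposed until they are censored by death", followed by leaving the practice, the practice ceasing to contribute data and the study end date of 29 March 2021. Death stands in the same list as administrative reasons for leaving.
- **Statistical methods (3.6)** says that a Cox model "will be used to measure time to event for first hospital admissions and mortality". Proportionality is to be checked with Kaplan-Meier plots and Schoenfeld residuals. If it fails, "alternatives such as restricted mean survival times models will be used". No truncation time and no treatment of death is given for that alternative.
- **Aims and objectives (2)** hypothesises that DSME affects both admissions and mortality. The objectives cover "all‐cause and cause‐specific hospital admissions, in adults with type 2 diabetes", as well as all-cause and cause-specific mortality and 3P-MACE.

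Competing risks, cumulative incidence and a composite of admission or death are not mentioned anywhere in the article.

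**The concern.** A patient who dies can no longer be admitted. Censoring that patient is harmless for one purpose: the Cox model then estimates the cause-specific hazard ratio, which compares admission rates among people still alive and not yet admitted.

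It is not harmless for summaries on the scale of absolute risk or time. Kaplan-Meier and an RMST built on it treat a censored patient as someone who would have gone on to be admitted at the same rate as those still observed. When censoring is by death, the result is admission-free time in a population where death does not occur. Even that reading needs death to be independent of admission risk given the covariates. This is doubtful here, since comorbidity and deprivation, which the article ties to mortality, are also adjusted for in the admission models.

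In this study deaths may also be removed at different rates in the two groups, because lower mortality with DSME is part of the hypothesis. If attenders live longer, they have more time in which to be admitted. A summary blind to death cannot show either the extra time alive or the extra admissions that come with it. The matter becomes practical if the proportional hazards check fails. With more than 21,000 attenders, a Schoenfeld test can reject for small departures.

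**Working it through.** The article states no figure to reproduce on this point, and it gives no admission or death rates. The rates below are therefore assumptions, used only to size the effect.

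**Inputs.** Follow-up T = 10 years (the longest the study period allows); event hazard l from 0.005 to 0.20 per year (assumed); death hazard m from 0.01 to 0.05 per year (assumed); all constant over time.

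**Formulas.**
- Death censored: 1-KM = 1 - exp(-lT); RMST = (1 - exp(-lT))/l. Neither contains m.
- Death as competing event: cumulative incidence CIF = l/(l+m) × (1 - exp(-(l+m)T)).
- Time alive and event-free: (1 - exp(-(l+m)T))/(l+m).
- Restricted mean time lost to the event: l/(l+m) × (T minus time alive and event-free).

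**Step 1: absolute risk at 10 years.**

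| l | m | 1-KM | CIF | Ratio |
|---|---|---|---|---|
| 0.005 | 0.05 | 4.9% | 3.8% | 1.27 |
| 0.02 | 0.03 | 18.1% | 15.7% | 1.15 |
| 0.10 | 0.01 | 63.2% | 60.6% | 1.04 |
| 0.10 | 0.03 | 63.2% | 56.0% | 1.13 |
| 0.10 | 0.05 | 63.2% | 51.8% | 1.22 |
| 0.20 | 0.01 | 86.5% | 83.6% | 1.03 |

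Over the whole assumed range the ratio runs from 1.03 to 1.27. It grows with the death rate and is somewhat larger for rarer events.

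**Step 2: the comparison between groups.** Suppose DSME has no effect on the admission hazard (l = 0.10 in both groups) but lowers mortality with a hazard ratio of 0.8: m = 0.030 in the never group and 0.030 × 0.8 = 0.024 in the ever group.

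- Death-censored RMST: (1 - exp(-1.0))/0.10 = 6.32 years in both groups; difference exactly 0.
- Time alive and admission-free: never (1 - exp(-1.30))/0.130 = 5.60 years; ever (1 - exp(-1.24))/0.124 = 5.73 years; difference 0.135 years.
- CIF of admission: never 0.10 × 5.596 = 56.0%; ever 0.10 × 5.731 = 57.3%; difference 1.35 percentage points.
- Restricted mean time lost to admission: never 0.10/0.130 × (10 - 5.596) = 3.39 years; ever 0.10/0.124 × (10 - 5.731) = 3.44 years; difference 0.055 years.

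With a mortality hazard ratio of 0.6 instead, the CIF difference is 2.75 points and the gain in time alive and admission-free is 0.275 years. The death-censored RMST difference is still 0.

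The competing-event summaries show more admissions in the ever group while the composite shows longer time alive and admission-free. Both are true in this example. That is why the admission result has to be read beside all-cause death.

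**The case against.** The strongest reply is that the article does not plan the faulty analysis outright. Several parts of this reply stand.

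- **Kaplan-Meier is named only as a check of proportional hazards.** A reader might infer that the planned curves are themselves wrong. They are not: with death censored they reflect the same hazard that the Cox model uses. Aalen-Johansen curves would be a poor replacement for that check because they also depend on the death hazard.
- **RMST is an example of an alternative and applies only if proportionality fails.** For all-cause mortality it is fully valid. A reader might infer that the error is bound to reach the main results; the wording does not support that.
- **Cause-specific Cox models that censor other-cause deaths are not stated.** The Cox sentence names first admissions and mortality. Cause-specific outcomes appear with the chi-squared tests and the mixed Poisson or negative binomial models.
- **The size is easily overstated.** With an assumed cluster event rate of 0.8% per year and death at 4% per year, one could set a death-censored RMST of 9.6 years against 7.9 years alive and event-free. Those are different quantities, and most of the gap is simply deaths. On restricted mean time lost, the same rates give 0.39 against 0.34 years.
- **Mortality is already a parallel outcome,** and crude proportions admitted and dying are compared directly, so part of the joint picture will be there.

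It may also be said that the follow-up sentence is loosely worded, since read literally it would censor deaths even where death is the outcome, and that building a fallback is a matter for a fuller plan. This does not dispose of the point. The article does fix a censoring rule that includes death and does name the fallback for first admission. An analyst who follows both as written obtains an RMST that ignores death, and nothing in the text directs otherwise.

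**Conclusion.** The point holds in a limited form. The stated censoring rule combined with the named fallback yields, for first admission, a summary of time that leaves out a terminal event which the study itself expects to differ by exposure. The same applies to any admission risk read off a Kaplan-Meier curve. The Cox models, if their admission hazard ratios are labelled cause-specific, the all-cause mortality analysis and the diagnostic plots stand as they are.

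The overstatement of absolute risk and the missed group difference are modest at the rates tried above, and both rest on assumed constant hazards, full 10-year follow-up and, for the group difference, an assumed mortality effect. They would change with the real rates. The change is worth making before analysis because it is cheap and settles what the fallback estimates; it is not a reason to doubt the main Cox analysis.

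**What to change.** In Statistical methods:

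1. Keep the Cox models and state that hazard ratios for admission are cause-specific, with death ending the time at risk.
2. Keep the Kaplan-Meier plots and Schoenfeld tests, described as checks of proportional hazards only.
3. Define the fallback for first admission as either restricted mean time alive and admission-free, or restricted mean time lost to admission with death as a competing event. Choose one in advance and fix the truncation time. RMST for all-cause mortality needs no change of definition.
4. Where absolute risk is reported for admission, 3P-MACE or cause-specific death, use Aalen-Johansen cumulative incidence. The competing event is death for admission, non-cardiovascular death for 3P-MACE, and other-cause death for cause-specific mortality. Show each beside all-cause mortality.

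In Data selection, reword the follow-up sentence so that death ends follow-up but is treated as an outcome or a competing event, separately from leaving the practice and the study end date.

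The cost is a few sentences, a little more analysis work with standard R code, and slightly smaller reported absolute risks. No new data are needed.
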